### 3.4 Tertiary (exploratory) Endpoints

- Time from catheter insertion to extubation
- Time from catheter insertion to first opioid analgesic provision following extubation
- Time from catheter insertion to mobilization
- ICU and hospital LOS
- Postoperative nausea and vomiting, measured via a 10-point visual analogue scale BID and antiemetic medication requirements up to 72 hours following catheter insertion
- Opioid requirements post-discharge as assessed by prescriptions provided at time of discharge and during post-discharge follow-up visit using both patient health record and direct patient recounting
- Chronic post sternotomy pain/disability and patient reported outcomes assessed at 3 months  $\pm$  4 weeks from surgery with McGill Pain Questionnaire as well as at 6 weeks  $\pm$  2 weeks and 3 months  $\pm$  4 weeks with the change in PROMIS 29 score (Attempts to obtain the 3-month data can continue for up to 6 months post-surgery before it will be considered a protocol deviation or the participant deemed lost-to-follow-up)

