### 5.2 Study Visits

#### *Visit S: Screening*

- Written informed consent
- Determination of eligibility
- Demographics, medical history, baseline medications including doses
- Physical examination, height and weight assessment, BMI
- Vital signs
- Laboratory assessments: CBC, creatinine/eGFR, electrolytes, coagulation testing
- Preoperative PROMIS 29 Score

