#### Non-Date Values

There will be no imputation of missing efficacy or safety data. However, the potential influence of rescue or intraoperative nerve blocks, delayed extubation, return to OR and death on MME efficacy endpoints will be explored in sensitivity analyses, described below.

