The analysis of covariance (ANCOVA) model with a fixed effects for treatment group, sex, BMI and intraoperative MMEs ( $<$ median,  $\geq$ median) will be used to analyze the primary efficacy endpoint. The least squares (LS) mean, standard errors, and 2-sided 95% confidence intervals (CIs) for each treatment group and for the mean difference compared to placebo will be estimated. The model will be fit assuming unequal variances for each treatment group. If substantial deviations from the model assumptions are observed, then supportive analyses, such as robust regression, non-parametric analyses, etc. will be considered. Missing values of predictors will either be imputed by the overall mean or most frequent category.

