### 3.4.2 Secondary Efficacy Endpoints

Pain score during the 72 hours following catheter insertion will be analyzed by a mixed model for repeated measures (MMRM), with random effects for intercept and time, fixed effects for treatment, sex, and intraoperative MMEs (<median, ≥median), and an unstructured covariance matrix.

The analysis of cumulative postoperative opioid use measured as MMEs from catheter insertion until discharge from hospital will be by the same methods as for the primary efficacy endpoint, including the joint model sensitivity analysis.

The analysis of incidence of delirium during the 72 hours following catheter insertion will be by logistic regression with fixed effects for treatment group, sex, and intraoperative MME (<median, ≥median). The treatment odds ratio (OR) and associated 95% confidence interval will be provided.

The analysis of Quality of Recovery-15 Scale administered 24-96 hours post-surgery will be by the same methods as for the primary efficacy endpoint.

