### 3.4.3 Exploratory Efficacy Endpoints

The analyses of time-to-event exploratory efficacy endpoints will be by proportional hazards models with fixed effects for treatment, sex, and intraoperative MMEs (<median, ≥median). The treatment hazard ratio (HR) and associated 95% CI will be provided. A cause-specific approach for competing terminal events (i.e., deaths) will be applied by censoring participants at the time of death. Cumulative incidences by treatment group will be estimated by Kaplan-Meier methods.

The analyses of incidence of postoperative nausea or vomiting will be by the same methods as pain score or delirium.

Opioid requirements post-discharge will be summarized by descriptive statistics.

The analyses of chronic post sternotomy pain/disability and patient reported outcomes assessed with the McGill Pain Questionnaire (3 months) and PROMIS 29 score (6 weeks, 3 months) will be by the same methods as for the primary efficacy endpoint.

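### PROMIS-29 at 3 months is analysed without the 6-week score, which can bias the 3-month contrast under some patterns of loss and modestly widens its interval

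*Combined protocol and SAP*

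**What the plan says.** - **Endpoint.** PROMIS-29 is collected before surgery (protocol section 5.2, screening visit: "Preoperative PROMIS 29 Score"), at 6 weeks and at 3 months. Protocol section 3.4 lists it as exploratory and describes it as a change: "with the change in PROMIS 29 score (Attempts to obtain the 3-month data can continue for up to 6 months post-surgery".
- **Method.** SAP section 3.4.3 sends it to the primary-endpoint method: "PROMIS 29 score (6 weeks, 3 months) will be by the same methods as for the primary efficacy endpoint". SAP section 3.4.1 defines that method as an ANCOVA "model with a fixed effects for treatment group, sex, BMI and intraoperative MMEs". It has no visit term, no preoperative score and no 6-week score.
- **Missing values.** SAP section 3.1.6: "There will be no imputation of missing efficacy or safety data". The only imputation is for covariates, in SAP section 3.4.1: "Missing values of predictors will either be imputed by the overall mean or most frequent category".
- **Contrast within the SAP.** The pain score over 72 hours, also a repeated measure, "will be analyzed by a mixed model for repeated measures (MMRM), with random effects for intercept and time" (SAP section 3.4.2).

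The SAP does not call the two PROMIS-29 analyses separate or complete-case, but both descriptions follow from these sections.

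**The concern.** The 3-month analysis discards information that the trial already holds. A patient with a 6-week score and no 3-month score leaves the 3-month contrast altogether, although the 6-week score says something about where that patient was heading. Some loss is foreseen: the protocol asks for up to two telephone numbers and lets attempts for the 3-month data run to 6 months.

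Two things are at stake. The 3-month difference may be biased if the patients who stop answering are selected on their 6-week state in a way that bears on the comparison. Its confidence interval is also somewhat wider than it need be. In addition, two unlinked analyses give no interval for how the treatment effect changes between the visits.

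**Working it through.** **Inputs from the documents.** The plan gives no figure for PROMIS-29. Its only sample-size figure, 133 per group, is for the 72-hour opioid endpoint (difference 10, SD 25, two-sided 5%, power 90%). It reproduces: 2 × (1.960 + 1.282)² × 25²/10² = 131.3, so 132 by the normal formula and 133 by the exact t calculation. It serves below only as an arm size. The 25% attrition rate belongs to the same calculation and is not a 3-month PROMIS-29 loss rate.

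**Assumed inputs.** The documents do not give the SD, the correlation r between the visits, the 3-month loss or what drives it. The ranges below are assumptions.

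**1. Precision under random loss.** If every patient has a 6-week score and a fraction L lacks the 3-month score, a joint model reduces the variance of the 3-month difference by r² × L.
- r = 0.5, L = 20%: 0.25 × 0.20 = 5%.
- r = 0.8, L = 30%: 0.64 × 0.30 = 19%.

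In interval width, the complete-case interval is wider by 1/√(1 − r²L) − 1.
- L = 10%: 0.5% (r = 0.3) to 3.4% (r = 0.8).
- L = 25%: 1.1% (r = 0.3) to 9.1% (r = 0.8).
- For example, with 170 per arm at 6 weeks, L = 25% and r = 0.6, the standard error is √(2/127.5) = 0.125 SD for complete cases and 0.125 × √(1 − 0.09) = 0.120 SD jointly, so the interval is 4.8% wider.

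**2. Bias when loss depends on the 6-week score alike in both arms.** Settings: SD 10, r 0.5 to 0.8, loss 20 to 30%, log-odds of loss 0.7 to 1.2 per SD of the 6-week score.

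| True effect at 6 weeks, 3 months (points) | Complete-case 3-month estimate | Joint model |
|---|---|---|
| 4, 1 | 0.40 to 0.87 | about 1.0 |
| 3, 3 | 2.56 to 2.91 | about 3.0 |
| 0, 3 | about 3.0 | not needed |
| 0, 0 | about 0 | about 0 |

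The bias in the first two rows runs from 3 − 2.91 = 0.09 to 1 − 0.40 = 0.60 points, or about 0.01 to 0.06 SD, and is towards zero. With 133 per arm and 25% loss, the standard error of the 3-month difference is 10 × √(2/(0.75 × 133)) = 1.4 points. Coverage of the nominal 95% interval stayed between 93.4% and 94.9% in these settings.

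**3. Bias when the dependence differs by arm.** Settings: r = 0.6, a true effect of 0.3 SD at both visits, odds ratio of loss 2 per SD where dependence exists.
- One arm only, 25% loss: +0.09 SD.
- One arm only, 10% loss: +0.04 SD.
- Opposite directions in the two arms, 25% loss: +0.18 SD.
- Loss completely at random: 0.00.

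A likelihood model that uses the 6-week score had bias of about 0 in each of these cases.

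**The case against.** The case for leaving the plan alone is substantial.

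- **Bias is not shown.** A reader might infer that the planned analysis does bias the 3-month result, or that it is unbiased only when loss is unrelated to the 6-week score. The documents support neither reading. They give no loss rate, correlation or missingness mechanism. Even loss that depends strongly on the 6-week score leaves the contrast unbiased if it works alike in both arms and the arms do not differ at 6 weeks. This stands.
- **The bias is small beside the noise.** When loss works alike in both arms, the bias is under half a standard error at the extreme setting (0.60 against 1.4). The worst proportional error (0.40 for a true 1.0) comes from pairing a large 6-week effect with a small 3-month one. This stands, although an early effect that fades is plausible for a 48-hour block.
- **The precision gain is a best case.** Patients who miss both calls add nothing, and including the preoperative score leaves less for the 6-week score to explain. This stands.
- **The endpoint is exploratory, and separate analyses by visit are conventional.** No listed objective asks for the change in effect between visits. This sets the priority. It does not make the discarded 6-week score useful to keep out, and the rationale in the amendment summary for adding the 6-week PROMIS-29 was partly to show a time trend.

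**Conclusion.** The point holds as a conditional risk with a modest cost in precision. SAP sections 3.4.3, 3.4.1 and 3.1.6 together exclude a known 6-week score from the 3-month contrast. Bias needs two things: loss that depends on the 6-week score, and either a treatment difference at 6 weeks or a dependence that differs by arm. Under the assumed ranges it is about 0.1 to 0.6 points on an SD of 10 when loss works alike in both arms. In the settings tried at 25% loss it is 0.09 to 0.18 SD when the dependence differs by arm. The avoidable variance is about 5 to 19% under random loss, and less in practice. All of these sizes rest on assumed correlation, loss and effects. PROMIS-29 is exploratory and the primary result is untouched, so the change is worth making because it is cheap.

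**What to change.** In SAP section 3.4.3, replace the PROMIS-29 ANCOVAs with one MMRM covering the 6-week and 3-month visits:

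- fixed effects for treatment, visit, treatment by visit, the preoperative PROMIS-29 score (the protocol endpoint is a change score) and the SAP covariates;
- an unstructured 2 × 2 covariance matrix;
- a report of the treatment difference at 6 weeks, at 3 months, and the change between them, each with a 95% confidence interval.

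The McGill Pain Questionnaire is measured only at 3 months and stays with the ANCOVA.

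The cost is SAP wording and a few lines of SAS, with no new data. The change should be made before database lock, by when SAP section 1 says the SAP will be final. The downside is reliance on missing at random: if loss depends on the unseen 3-month state beyond what the 6-week score and covariates explain, the MMRM can be biased too.

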### 3.4.4 Subgroup Analysis

The primary efficacy endpoint will be analyzed by the following subgroups:

- Age (<median, ≥median)
- Race/ethnicity
- Sex (male, female)
- Diabetes status
- BMI (<median, ≥median)
- Type of Operation
- Intraoperative MMEs (<median, ≥median)

An ANCOVA model with a fixed effects for the treatment group, sex, intraoperative MMEs, subgroup (not applicable for sex and intraoperative MMEs subgroup analyses) and the interaction between treatment group and subgroup will be applied. The least squares (LS)

mean, standard errors, and 2-sided 95% confidence intervals for each treatment group and for the mean difference compared to placebo, within each level of the subgroup, will be estimated.

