### 3.5 Randomization Procedure

Randomization will be performed via a centralized, web-based platform that uses permuted blocks of varying sizes. Randomization will be stratified by site and patient sex. Dedicated unblinded individuals at each site who are responsible for preparing the assigned blinded bags of ropivacaine and saline will be provided with a randomization code list. Details on participant allocation and the randomization code lists will not be shared with the blinded study team members.

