## **7. Statistical Analysis and Sample Size Calculation**

For the primary analysis, we will perform linear regression, adjusted for sex (clinical stratification factor) and intraoperative opioid MME to assess the comparison between trial groups, with a P-value threshold of 0.05 being considered significant. If residuals indicate substantial violations of the linear regression assumptions, alternate methods will be attempted, such as analyzing log-transformed data, using bootstrap hypothesis testing or two-sample t-tests without equal variance. A modified intention-to-treat analysis will be employed, including only patients in whom a block catheter was placed, and a dose of study drug was administered. The time-to-event outcomes will be modelled simultaneously using a multistate framework. This approach will handle competing risks, such as death, and treat other non-fatal events, that could be related to each other, as intercurrent events. Sensitivity analyses using complete intention-to-treat and per protocol populations will also be conducted. Categorical data will be summarized by frequencies and percentages, and continuous variables by means and standard deviations (plus medians and interquartile ranges for non-symmetric data).

In order to detect a mean difference of 10 MMEs, assuming a standard deviation of 25 and an alpha value of 0.05, a sample size of 133 participants per group would be required to provide a power of 90%. Assuming an attrition rate of 25%, approximately 340 patients will need to be randomized for the primary modified intention-to-treat analysis.

Pre-specified subgroup analyses of the primary outcome include:

- Age
- Race/Ethnicity
- Sex/Gender
- Diabetes status
- BMI
- Type of operation
- Site

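### Site, a randomisation stratum, is in none of the SAP's efficacy models, and the subgroup ANCOVA drops the BMI term that the primary ANCOVA carries

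*Combined protocol and SAP*

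**What the plan says.** **Randomisation.** Protocol 3.5: "Randomization will be stratified by site and patient sex".

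**Protocol primary model.** Section 7: "we will perform linear regression, adjusted for sex (clinical stratification factor) and intraoperative opioid MME". Sex is justified there as a stratification factor. Site, the other stratification factor, is not in the model, and neither is BMI. Site does appear in that section's list of subgroups.

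**SAP primary model.** SAP 3.4.1 specifies an ANCOVA with "fixed effects for treatment group, sex, BMI and intraoperative MMEs", the last split at its median. Whether BMI is continuous or categorised is not stated. The joint-model sensitivity analysis reuses this ANCOVA.

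**SAP subgroup model, same endpoint.** SAP 3.4.4: "An ANCOVA model with a fixed effects for the treatment group, sex, intraoperative MMEs, subgroup", plus the treatment-by-subgroup interaction. BMI enters only when it is itself the subgroup, split at the median. The separate subgroup term is waived for the sex and intraoperative-MME subgroups, because those variables are already in the model; BMI gets no such waiver. Site is not on the SAP's subgroup list.

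**Other SAP models.**
- Opioid use to discharge and QoR-15 (3.4.2), and the McGill and PROMIS-29 analyses (3.4.3), follow the primary methods and so include BMI.
- The pain mixed model (3.4.2) has "fixed effects for treatment, sex, and intraoperative MMEs".
- Delirium (3.4.2) uses "logistic regression with fixed effects for treatment group, sex, and intraoperative MME".
- The time-to-event models (3.4.3) adjust for sex and intraoperative MME.

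None of these contains site.

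**The concern.** An analysis should normally reflect the factors used to stratify randomisation. Balancing the arms within sites removes site differences from the treatment comparison. A model without site still counts those differences as residual noise, so the reported standard error is too large and the test conservative to the extent that site predicts the outcome. Such an effect is plausible here, because each of the four sites keeps its own anaesthetic and postoperative analgesic routine (protocol 3.1, SAP 2.2.1). The documents do not quantify it.

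BMI is a second matter. It is not a stratification factor, so leaving it out forgoes real precision if it predicts opioid use. It is in the main analysis of the primary endpoint but not in the subgroup analysis of that endpoint, nor in the protocol's primary model. Subgroup estimates will be read beside an overall estimate that was adjusted differently, and a reader holding both documents finds two primary models.

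**Working it through.** **1. Covariates side by side (in addition to treatment).**

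| Model | Sex | Intraop. MME | BMI | Site |
|---|---|---|---|---|
| Protocol 7, primary | yes | yes | no | no |
| SAP 3.4.1, primary and its sensitivity analysis | yes | yes | yes | no |
| SAP 3.4.2–3.4.3, analyses following the primary methods | yes | yes | yes | no |
| SAP 3.4.4, subgroup | yes | yes | only as the BMI subgroup | no |
| SAP 3.4.2, pain | yes | yes | no | no |
| SAP 3.4.2, delirium | yes | yes | no | no |
| SAP 3.4.3, time-to-event | yes | yes | no | no |

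**2. The plan's own figure.** Inputs from protocol Section 7 and SAP 2.2.2: difference 10 MME, SD 25, two-sided alpha 0.05, power 90%. The normal approximation is n = 2(1.96 + 1.2816)² × 25²/10² = 131.3, so 132 per group. The t-test gives 132.3, so 133. The stated 133 reproduces, with power 0.901. It uses an unadjusted SD, so the planned power does not depend on BMI or site.

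**3. Size in the linear models.** Let R² be the share of the remaining outcome variance that the omitted terms explain. The documents give no value, so R² is assumed. The standard error of the treatment difference falls by the factor √(1 − R²).

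- Overall, 133 per group: 25 × √(2/133) = 3.066 MME before adjustment.
- One level of an evenly split subgroup, 66.5 per group: 25 × √(2/66.5) = 4.336 MME.

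| Assumed R² | √(1 − R²) | Reduction in SE | Overall SE | Half-sample SE |
|---|---|---|---|---|
| 0 | 1.000 | 0% | 3.066 | 4.336 |
| 0.02 | 0.990 | 1.0% | 3.035 | 4.292 |
| 0.05 | 0.975 | 2.5% | 2.988 | 4.226 |
| 0.10 | 0.949 | 5.1% | 2.908 | 4.113 |

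For a single covariate with assumed partial correlation 0.1, 0.2 or 0.3 (R² = 0.01, 0.04, 0.09), power at 133 per group would be 90.4%, 91.3% or 92.6%, against 90.1%.

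**4. What it means for site.** If the whole R² came from site and stratification balanced the arms well, the unadjusted test would in effect use the critical value 1.96/√(1 − R²): 1.980, 2.011 or 2.066. The actual two-sided error rate would be about 4.8%, 4.4% or 3.9% instead of 5%. The error is on the conservative side.

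**5. Cost of adding site.** Four sites need three terms. With 266 participants, the primary ANCOVA (intercept, treatment, sex, one BMI term, intraoperative MME) leaves 266 − 5 = 261 residual degrees of freedom, or 258 with site. If site removed no residual sum of squares at all, the standard error would rise by the factor √(261/258) = 1.006.

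**6. Why this stops at the linear models.** The √(1 − R²) rule does not carry over to logistic or proportional hazards models. In a simulation of a delirium-type outcome (600 runs per setting, 133 per arm, intercept −1.7 and treatment odds ratio 0.5, all assumed), the mean standard error of the log odds ratio without and with a prognostic covariate was 0.402 and 0.404, 0.395 and 0.400, and 0.379 and 0.392, for covariate odds ratios of 1.2, 1.5 and 2.0 per SD. Power moved by at most about 1.5 points, within simulation error. Adjustment there mainly changes which odds ratio is estimated.

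**The case against.** The best defence is that nothing here is wrong in the sense of bias, and that the gain is hypothetical. Neither document gives an association of site or BMI with opioid use; at R² = 0 nothing is gained, and the sample size does not rely on either covariate. That stands, and it keeps the point small.

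Four stronger readings are tempting and are not supported.

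- **That precision is lost as a matter of fact, in every model.** The loss depends on an unreported association, and the argument covers the linear models only.
- **That pain, delirium and time-to-event outcomes must carry BMI because the primary does.** They are different endpoints and need not share its covariates. QoR-15 and opioid use to discharge already have BMI through the primary methods.
- **That a common covariate set would make subgroup and overall results agree exactly.** It would not: the subgroup model adds a subgroup main effect and an interaction, so its estimates need not average to the overall one. Alignment removes one avoidable difference only.
- **That the trial has two competing primary models.** The SAP (06FEB2026) is later than the protocol (30 OCT 2025) and states that it describes the methods to be implemented, so most readers would follow it. What is missing from the text available is a sentence saying so and giving the reason for adding BMI.

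It can also be said that site is absent from every model and so is no inconsistency between analyses. True, but the case for site rests on how the trial randomises, not on a mismatch.

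**Conclusion.** The point holds as a minor one. Site is a stratification factor that no SAP efficacy model uses, and BMI is in the primary ANCOVA but not in the subgroup ANCOVA of the same endpoint or in the protocol's primary model. Estimates are valid either way. In the linear models the avoidable part of the standard error is 0% if the omitted terms predict nothing, and 1.0%, 2.5% or 5.1% at assumed R² of 0.02, 0.05 or 0.10. These rest on assumed R² values, 133 analysed per group, and SD 25 as the variation before the extra terms. Nothing is claimed about precision for delirium or the time-to-event outcomes.

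**What to change.** In the SAP:

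1. **3.4.1:** add site as a fixed effect to the primary ANCOVA, and state whether BMI is continuous or split. The analyses that follow the primary methods (sensitivity analysis, opioid use to discharge, QoR-15, McGill, PROMIS-29) then inherit site.
2. **3.4.4:** use the same set (treatment, sex, site, BMI, intraoperative MME) plus subgroup and interaction. Extend the existing waiver to the BMI subgroup so that BMI is not entered twice.
3. **3.4.2:** add site to the pain mixed model.
4. State that the SAP model supersedes protocol Section 7, with the reason for adding BMI.

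Leave the covariates of the delirium and time-to-event models as they are; BMI need not be added there.

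The cost is wording and about three degrees of freedom. Site and BMI are already in the SAP 3.3.3 baseline table, and SAP 3.4.1 imputes missing predictors, so no participant is lost. One detail to settle: the logistic part of the joint sensitivity model takes the ANCOVA's fixed effects, so the SAP should say whether site is kept there if events are few. The change should be made before database lock and unblinding.
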